## Adverse Event Relationship to Study Product

The relationship of all AEs to study product will be assessed as follows:

- - Definitely related: adverse event and administration of study agent are related in time, and a direct association can be demonstrated with the study agent.
  - Probably related: adverse event and administration of study agent are reasonably related in time, and the adverse event is more likely explained by the study agent than by other causes.
  - Possibly related: adverse event and administration of study agent are reasonably related in time, and the adverse event can be explained equally well by causes other than the study agent.
  - Probably not related: a potential relationship between administration of study agent and adverse event could exist, but is unlikely, and the adverse event is most likely explained by causes other than the study agent.
  - Not related: the adverse event is clearly explained by another cause unrelated to administration of the study agent. Reportable events must have documentation to support the determination of “not related”.

The assessment for AE relationship to study product must be conducted while the reviewer is blinded to randomization allocation for the child in question.

The initial determination of AE relationship to study product will be made by study staff with as needed consultation with the local PI. A study team medical officer will review determinations of AE relationship and assign the final relationship determination for all Grade 4 and 5 events, including all SAEs. For any death in the study, an independent medical officer will make the final determination of relationship to study product.

## Grading Severity of Events

All adverse events will be graded by the widely used DAIDS AE Grading Table Version 1.0, December 2004; clarification August 2009. This grading table is now adopted by the U.S. Food and Drug Administration (U.S. FDA) for AE reporting. This table is available at: <http://rcc.tech-res.com/Document/safetyandpharmacovigilance/Table_for_Grading_Severity_of_Adult_Pediatric_Adverse_Events.pdf>

## Safety Reporting

All SAEs must be reported by the site to the medical officers and Sponsor within 24 hours. Attribution with regard to relationship to study product will only be reported for AE grades 2 or above and for all SAEs.Prior to study unblinding, any Grade 4 local or systemic reactogenicity symptom or AE, described by the site staff as possibly, probably, or definitely related to the study product, or any Grade 5 event requires immediate notification by the site to the study coordinator and co-PIs. The co-PIs will convene within 24 hours by teleconference and decide whether the event necessitates a pause in further enrollment. If the team cannot convene to review the event within 24 hours, the medical officer will make the final decision.

Reporting requirements for the IRB/IEC will be followed as appropriate.

## Study Discontinuation

The trial may be discontinued at any time by the protocol team, sponsor, funding agency, Malawi regulatory authorities, or institutional review board/ethics committee. Please refer to Section 5.1 on Data Analysis, specifically the section on Analytical Methodology for Interim Analyses for more detail on the decision to discontinue the trial for safety.

# STATISTICAL DESIGN AND ANALYSIS

## DATA ANALYSIS

## Overview and General Design

In brief, we plan to conduct a facility-based, double-blinded, individually randomized, non-inferiority trial of 3 days (intervention) versus 5 days (control) of oral amoxicillin DT for chest-indrawing pneumonia.

The study will include 2,000 HIV-1 seronegative children aged 2 to 59 months presenting with chest-indrawing pneumonia at KCH or BDH in Lilongwe, Malawi. The treatment groups for the chest-indrawing pneumonia study will include treatments with oral amoxicillin DT in two divided doses based on age bands (500 mg/day for children 2 months up to 12 months, 1000 mg/day for children 12 months up to 3 years, and 1,500 mg/day for children 3 years up to 5 years of age) for 3 days (+ 2 days placebo) versus 5 days. Treatment will be block randomized (with concealed block size) within each age group to achieve a 1:1 ratio of intervention and control.

## Randomization and Blinding Procedures

Randomization will be perform as 1:1 based on permuted blocks of concealed size within strata defined by age groups (2 up to 12 months, 12 up to 36 months, 36 up to 59 months). Three randomization lists (one for each age group) will be provided by the statisticians to the study pharmacy. The study pharmacists and the Protocol Statisticians will be the only individuals who have access to the treatment assignment for each study patient. Patients, their caregivers and all other study personnel will remain blinded during the course of the study until the primary results manuscript is finalized.

The Sponsor does not anticipate any type of emergency situation where unblinding a child’s randomization allocation would be necessary. If an unanticipated need to unblind a child’s randomization allocation for reasons of participant safety arises during the course of the study, the site investigators, sponsor, and IRB/IEC will be notified and the instance will be documented.

## Objectives and Endpoints

In this study, the primary null hypothesis will be that the primary outcome of treatment failure at 6 days in those who received 3 days of amoxicillin DT (and 2 days placebo DT) is inferior (non-inferior in the alternative hypothesis) to those who received 5 days of amoxicillin DT for the treatment of chest-indrawing pneumonia in children aged 2–59 months. Eligible children will be randomly assigned to receive oral amoxicillin DT twice daily for 3 days (and 2 days placebo) in the intervention group and for 5 days in the control group. The children will be evaluated on day 4, after 3 days of treatment, to assess response to treatment and on day 6, after 5 days of treatment, to assess treatment failure; by this time point, they would have received all their treatment and we would expect them to either be cured or to have failed treatment. They will also be evaluated on days 2 and 14 to assess response to treatment. If a child becomes ill again after the chest-indrawing initially returned to normal, they will be encouraged to return between days 6 and 14 to assess for relapse.

The primary outcome will be treatment failure before or on day 6 for intervention and control groups. Secondary outcomes include: (a) clinical relapse between days 6 and 14 if treatment failure was not present before or on day 6, (b) combined rates of clinical relapse and treatment failures before or on day 14, (c) AEs and SAEs, (d) prevalence of malaria among children with cough and/or difficulty in breathing AND fever, (e) differential treatment response among children with wheeze at screening, (f) differential treatment response among children with oxygen saturation <93% by pulse oximetry at baseline, (g) differential treatment response among children with MUAC-defined moderate malnutrition at baseline, (h) differential treatment response among children with very fast-breathing for age at baseline, and (i) differential treatment response by age. Refer to Section 3 on Hypothesis, Objectives, and Endpoints for full description of all objectives.

- *Treatment failure* will be defined as development of any of the following criteria during the specified time periods:
  - Any time before or on day 6: WHO IMCI danger signs, severe respiratory distress (e.g., grunting, nasal flaring, head nodding, or severe chest-indrawing), oxygen saturation by pulse oximetry < 90%, missing 3 or more doses due to vomiting, change in antibiotics prescribed by a study clinician, or death.
  - At or after initial hospitalization discharge assessment (between 42 and 60 hours post-enrollment): documented axillary temperature > 38 ºC with chest-indrawing.
  - At day 6 outcome assessment: persistence of chest-indrawing, or axillary temperature > 38 ºC.
  - For the purposes of this protocol, children who do not fail on assessment at day 6 will be considered clinically cured. Loss to follow-up or withdrawal from the study at any time after enrollment and before the day 14 follow-up visit will be considered missing outcome data for that respective time point.
- *Clinical relapse* will be defined as recurrence of signs of chest-indrawing pneumonia, severe respiratory distress (e.g., grunting, nasal flaring, head nodding, or severe chest- indrawing) or severe disease after day 6 among those who did not have treatment failure at or by day 6.

Recruitment and follow-up is expected to continue until the maximum sample size is achieved. For the chest-indrawing pneumonia study a total of 2,000 children (1,000 per treatment group) will be enrolled. We are assuming a treatment failure rate of 8% in the 5-day control group and a relative 1.5 non-inferiority margin. Figure 3 shows the maximum true failure rate in the 3-day treatment group in reference to various possible failure rates in the 5-day treatment group and a 1.5 relative non-inferiority margin (50% relative increase in failure rate) that would result in a 95% confidence interval at maximum enrollment which excludes the non-inferiority margin. The figure also indicates the power the study has to show non-inferiority if the failure rates are exactly the same in the two treatment groups for various possible failure rates. Of note, the estimated power is adjusted for a 5% loss to follow-up rate in each of the arms. This is considered conservative with respect to the multiple imputation procedure that will be used to account for missing outcome values.

**Figure 3.** Chest-indrawing pneumonia failure rates

Note:

- Blue, solid circles, blue number below: Potential failure rates for the 5-day treatment group.
- Blue, solid circles, blue number above: Power to detect the alternative of exactly equal failure rates in both treatment groups
- Green, hollow squares: Non-inferiority margins (depending on assumed failure rate in the 5-day treatment group.
- Hollow, red circles: Maximum true failure rate for the 3-day treatment group observed at maximum enrollment of 2,000 children (1,000 children in each control and treatment groups and assuming 5% loss to follow-up in each of the groups resulting in 1,900 children with complete outcome data for the primary analysis) for which the 95% confidence interval excludes the non-inferiority margin. For example, for a failure rate of 8% in the 5-day treatment group (assumed for the chest-indrawing pneumonia), the true failure rate in the 3-day treatment group can be 9.7% (1.7% above the control group) and can still rule out with high confidence a failure rate of 12% in the 3-day treatment group.

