For adherence, note that completing 80% of all scheduled dose administrations is considered to meet treatment completion criteria (i.e., 8 out of 10 doses over the 5 days). If doses are missed due to non-adherence, no study action will be taken beyond documenting the missed doses and counseling the caregiver on adherence and study product administration. If a child vomits within 30 minutes of a dose, one repeat dose may be attempted. If a child vomits within 30 minutes after 3 or more scheduled (i.e., not repeat) dose administrations, this will be considered a treatment failure and that child will be referred to care for a work-up of the vomiting cause and will be prescribed a course of second-line antibiotics.

All follow-up visit procedures will be documented in the appropriate study forms. Clinical assessments and findings will also be documented in the child’s medical record, as appropriate.

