The same treatment failure definition as above will be used for these subgroups analysis. Subgroup classification will be obtained from the screening data.

Additional subgroups not defined in either the approved protocol or statistical analysis plan will be considered post-hoc. Statisticians will keep a list of post-hoc analysis requested by investigators during the study duration.

1. **ENDPOINTS AND COVARIATES**

*6.1 Primary endpoint*

The primary endpoint will be the proportion of children failing treatment, defined as the development of any of the following before or on day 6:

- - - - WHO Integrated Management of Childhood Illness (IMCI) danger signs
      - Severe respiratory distress (e.g., grunting, nasal flaring, head nodding, or severe chest-indrawing).
      - Oxygen saturation < 90% by pulse oximetry
      - Vomiting within 30 minutes of 3 or more scheduled (i.e., not repeat) dose administrations of study product
      - Change in antibiotics prescribed by a study clinician (e.g., switch to a second-line antibiotic or prescription for onset of a co-infection)
      - Death

At or after initial hospitalization discharge assessment (between 42 and 60 hours post-enrollment):

- - - - Documented axillary temperature > 38 ºC with chest-indrawing

At day 6 outcome assessment:

- - - - Documented axillary temperature > 38 ºC
      - Chest-indrawing

The primary endpoint will be calculated from day 2, 4, 6 follow-up forms. The presence of any of the above criteria at any point prior to day 6 will constitute treatment failure. In addition to the overall treatment failure rate by day 6, we will also examine the treatment failure rates at 2 and 4 for both treatment arms.

Covariates for primary analysis: In addition to the treatment variable, the primary analysis will include (be adjusted for) the following covariates: age (2 months up to 12 months, 12 months up to 3 years, 3 years up to 5 years) and site (Bwaila District Hospital and Kamuzu Central Hospital). Of note, these are the same variables that are used for stratifying randomization. In addition, we will adjust for gender, as gender has been shown to be related to pneumonia mortality[1].

*6.2 Secondary endpoints*

The trial has the following several secondary endpoints

1. Proportion of children with clinical relapse between treatment failure assessment and day 14 follow-up visit among all children without treatment failure before or on day 6.

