APPENDIX A – Tables

Table 1: Patient and Clinical Characteristics at Enrollment

|  | Arm A  (n=X) | Arm B  (n=X) | Overall  (n=X) |
| --- | --- | --- | --- |
| Age |  |  |  |
| Median (IQR) | xx (xx) | xx (xx) | xx (xx) |
| 2-12 months, n (%) | xx (xx%) | xx (xx%) | xx (xx%) |
| 13-36 months, n (%) | xx (xx%) | xx (xx%) | xx (xx%) |
| 37-59 months, n (%) | xx (xx%) | xx (xx%) | xx (xx%) |
| Sex |  |  |  |
| Male, n (%) | xx (xx%) | xx (xx%) | xx (xx%) |
| Female, n (%) | xx (xx%) | xx (xx%) | xx (xx%) |
| Weight (kg) |  |  |  |
| Median (IQR) | xx (xx) | xx (xx) | xx (xx) |
| Height/length (cm) |  |  |  |
| Median (IQR) | xx (xx) | xx (xx) | xx (xx) |
| Weight-Height Z-Score |  |  |  |
| Median (IQR) | xx (xx) | xx (xx) | xx (xx) |
| Vital Signs, median (IQR) |  |  |  |
| Axillary Temperature (°C) | xx (xx) | xx (xx) | xx (xx) |
| Oxygen Saturation (%) | xx (xx) | xx (xx) | xx (xx) |
| Respiratory Rate (breaths/min) | xx (xx) | xx (xx) | xx (xx) |
| Pulse Rate (beats/min) | xx (xx) | xx (xx) | xx (xx) |
| Caregiver Assessment |  |  |  |
| Diarrhea | xx (xx%) | xx (xx%) | xx (xx%) |
| Fever | xx (xx%) | xx (xx%) | xx (xx%) |
| Cough | xx (xx%) | xx (xx%) | xx (xx%) |
| Fast/difficult breathing | xx (xx%) | xx (xx%) | xx (xx%) |
| Chest-indrawing | xx (xx%) | xx (xx%) | xx (xx%) |
| Nasal blockage | xx (xx%) | xx (xx%) | xx (xx%) |
| Runny nose | xx (xx%) | xx (xx%) | xx (xx%) |
| Poor feeding | xx (xx%) | xx (xx%) | xx (xx%) |
| Feeling cold to touch | xx (xx%) | xx (xx%) | xx (xx%) |
| Vomiting | xx (xx%) | xx (xx%) | xx (xx%) |
| Lethargy | xx (xx%) | xx (xx%) | xx (xx%) |

Table 2: Treatment Failure Prior to Day 6

|  | Arm A  (n=X) | Arm B  (n=X) | Overall  (n=X) |
| --- | --- | --- | --- |
| Treatment Failure On or Before Day 6 | xx (xx%) | xx (xx%) | xx (xx%) |
| Reason for Treatment Failure |  |  |  |
| WHO Danger Signs | xx (xx%) | xx (xx%) | xx (xx%) |
| Hypoxia (SaO2 < 90%) | xx (xx%) | xx (xx%) | xx (xx%) |
| Axillary Temperature ≥ 38 in absence of  diagnosed co-infection w/ fever symptoms | xx (xx%) | xx (xx%) | xx (xx%) |
| Change in antibiotics | xx (xx%) | xx (xx%) | xx (xx%) |
| Prolonged hospitalization or re-admission  due to pneumonia | xx (xx%) | xx (xx%) | xx (xx%) |
| Chest-indrawing | xx (xx%) | xx (xx%) | xx (xx%) |
| Death | xx (xx%) | xx (xx%) | xx (xx%) |

Table 3: Treatment Failure Prior to Day 6 for Pre-Specified Subgroups

|  | Arm A  (n=X) | Arm B  (n=X) | Overall  (n=X) |
| --- | --- | --- | --- |

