| Malaria Positive Test, n (%) | xx (xx%) | xx (xx%) | xx (xx%) |
| Malaria Negative Test, n (%) | xx (xx%) | xx (xx%) | xx (xx%) |
|  |  |  |  |
| Wheeze at baseline, n (%) | xx (xx%) | xx (xx%) | xx (xx%) |
| No wheeze at baseline, n (%) | xx (xx%) | xx (xx%) | xx (xx%) |
|  |  |  |  |
| Age 2-12 months, n (%) | xx (xx%) | xx (xx%) | xx (xx%) |
| Age 13-36 months, n (%) | xx (xx%) | xx (xx%) | xx (xx%) |
| Age 37-59 months, n (%) | xx (xx%) | xx (xx%) | xx (xx%) |

Table 4: Clinical Relapse on Day 14 by Treatment Arm

|  | Arm A  (n=X) | Arm B  (n=X) | Overall  (n=X) |
| --- | --- | --- | --- |
| Clinically Cured on Day 6 | xx | xx | xx |
| Clinical Relapse on Day 14, n (%) | xx (xx%) | xx (xx%) | xx (xx%) |
| Clinical Relapse Criteria or Danger Signs |  |  |  |
| Convulsions | xx (xx%) | xx (xx%) | xx (xx%) |
| Lethargic or unconscious | xx (xx%) | xx (xx%) | xx (xx%) |
| Unable to feed or drink |  |  |  |
| Vomits everything | xx (xx%) | xx (xx%) | xx (xx%) |
| Stridor when calm | xx (xx%) | xx (xx%) | xx (xx%) |
| Hypoxia (SaO2 < 90%) | xx (xx%) | xx (xx%) | xx (xx%) |
| Axillary Temperature ≥38 in absence of  diagnosed co-infection with fever symptons |  |  |  |
| Change in antibiotics |  |  |  |
| Prolonged hospitalization or re-admission  due to pneumonia |  |  |  |

References

1. Marzia Lazzerini, Nadine Seward, [name], Rosina Banda, Sophie Sinyeka, Gibson Masache, Bejoy Nambiar, Charles Makwenda, Anthony Costello, Eric D McCollum, Tim Colbourn, 2016, Mortality and its risk factors in Malawian children admitted to hospital with clinical pneumonia, 2001–12: a retrospective observational study, Lancet Global Health, 4, e57-68.
2. Scott Emerson, John Kittelson and Dan Gillen (2014). RCTdesign: Design, monitoring, and analysis of sequential clinical trials.. R package version 1.1.
3. Rubin DB. Multiple Imputation for Nonresponse in Surveys. Hoboken, NJ: Wiley Inc; 1987
4. R Core Team (2013). R: A language and environment for statistical computing. R Foundation for Statistical Computing, Vienna, Austria. URL http://www.R-project.org/.

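### Treatment failure and relapse are stated inconsistently across the protocol, SAP 6.1 and the SAP table shells, and SAP 6.1 contradicts its own time windows

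*Combined protocol and SAP*

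**What the plan says.** **Time windows.** Protocol 3, Protocol 5.1 and SAP 6.1 share a three-part structure. Danger signs, severe respiratory distress, saturation below 90%, the vomiting criterion, antibiotic change and death count at any time up to day 6. Fever combined with chest-indrawing counts from the discharge assessment at 42 to 60 hours. Fever alone or chest-indrawing alone counts at day 6. After this list SAP 6.1 adds: "The presence of any of the above criteria at any point prior to day 6 will constitute treatment failure".

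**Vomiting.** Protocol 3 and SAP 6.1 count "Vomiting within 30 minutes of 3 or more scheduled (i.e., not repeat) dose administrations of study product", and Protocol 4.6 (Follow-Up Visits) has the same rule. Protocol 5.1 counts "missing 3 or more doses due to vomiting". Protocol 4.6 also says: "If a child vomits within 30 minutes of a dose, one repeat dose may be attempted".

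**Day 6 signs.** Protocol 5.1 reads "At day 6 outcome assessment: persistence of chest-indrawing, or axillary temperature > 38 ºC". Protocol 3 and SAP 6.1 list "Documented axillary temperature > 38 ºC" and chest-indrawing, without requiring persistence.

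**Table 2 (SAP Appendix A).** The fever row is set at 38 or above and applies only without a diagnosed febrile co-infection. There is a row for "Prolonged hospitalization or re-admission" due to pneumonia. There is no row for severe respiratory distress or for vomiting.

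**Relapse.** Protocol 5.1 defines it as recurrent signs of chest-indrawing pneumonia, severe respiratory distress, or severe disease after day 6. SAP 6.2 names the endpoint without defining it. Table 4, under "Clinical Relapse Criteria or Danger Signs", lists danger signs, stridor, hypoxia, fever, antibiotic change and prolonged stay or re-admission. It has no row for chest-indrawing or severe respiratory distress.

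**The concern.** The primary endpoint should classify each child the same way whichever section the analyst opens. Here a child can be constructed who is classified differently for each discrepancy. If the choice between wordings is left open until data are in hand, it becomes an analysis decision made after the fact.

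The SAP 6.1 sentence has the widest potential reach. Chest-indrawing is an entry criterion, so a rule that counts it alone at day 2 or day 4 could take in children who are simply still recovering. SAP 6.1 also plans to report failure rates at those two visits, so the programmer has to settle the question for those rates too.

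For relapse, the SAP alone does not say what to count, and its only list leaves out the signs that define relapse in the protocol.

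**Working it through.** **1. Texts side by side, with a child for whom each pair differs**

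| Component | One text | Other text | Child classified differently |
|---|---|---|---|
| Window for chest-indrawing alone | SAP 6.1 list, Protocol 3, Protocol 5.1: day 6 | SAP 6.1 closing sentence: any point before day 6 | Indrawing without fever at day 2 or 4, gone by day 6 |
| Vomiting | Protocol 3, 4.6, SAP 6.1: 3 scheduled doses vomited | Protocol 5.1: 3 doses missed | Vomits 3 scheduled doses, keeps the repeats down, antibiotic not changed |
| Day 6 chest-indrawing | Protocol 3, SAP 6.1: present | Protocol 5.1: persistent | Indrawing resolves, then returns by day 6 |
| Fever | All three definitions: above 38, no exception | Table 2: 38 or above, no febrile co-infection | Exactly 38.0, or febrile with a diagnosed co-infection |
| Prolonged stay or re-admission | In none of the definitions | Table 2 row | Kept in or re-admitted without meeting a listed criterion |
| Relapse | Protocol 5.1: recurrent indrawing signs, distress, severe disease | Table 4: neither of the first two; fever, antibiotic change and stay added | Indrawing returns at day 10 with no other sign |

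The first three rows are conflicts between governing texts. The fever and prolonged-stay rows arise only from the Table 2 shell. The relapse row sets the protocol definition against the Table 4 shell, because SAP 6.2 gives none.

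**2. The plan's power figure.** Inputs: 8% in both arms, margin factor 1.5 (4.0 points), 950 per arm, one-sided 0.025 (Protocol 4.5, Protocol 5.1).

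Power = Φ(0.04 / √(2 × 0.08 × 0.92 / 950) − 1.96) = Φ(3.213 − 1.96) = 89.5%. The plan states 88%, so the figure is reproduced to within 2 points.

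**3. Why the definition matters even if it affects both arms equally.** The margin is half the 5-day failure rate. By the same formula with equal rates:

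- 6%: margin 3.0 points, power 78.6%
- 8%: margin 4.0 points, power 89.5%
- 10%: margin 5.0 points, power 95.3%

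The final-analysis column of SAP Table 1 (section 7.2) shows the same. The largest passing excess is 8.3 − 7.0 = 1.3 points at a 7% control rate, 9.7 − 8.0 = 1.7 at 8%, and 11.0 − 9.0 = 2.0 at 9%. An excess of 1.5 points therefore fails at 7% and passes at 8%.

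**4. Illustration with assumed counts** (unadjusted, 950 per arm; upper limit = difference + 1.96 × √[(p₅(1 − p₅) + p₃(1 − p₃)) / 950]):

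- 76 vs 90 failures (5-day vs 3-day; 8.00% vs 9.47%): 1.47 + 2.54 = 4.01 points, margin 4.00. Not shown.
- 81 vs 95 failures (8.53% vs 10.00%): 1.47 + 2.61 = 4.08 points, margin 4.26. Shown.

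Five more failures in each arm leave the difference unchanged and reverse the conclusion. The tipping point depends on the interval. This plain interval passes up to 9.46% at an 8% control rate, whereas the plan states 9.7% and would already pass the first pair. The counts show the mechanism and are not a forecast.

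**The case against.** Much can be said for the plan, and three stronger readings do not hold.

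**Vomiting.** A reader might infer that the child who vomits three scheduled doses and keeps the repeats down is a failure in one text and a success in the other. Protocol 4.6 says that child is to be prescribed second-line antibiotics, and Protocol 5.1 counts an antibiotic change by a study clinician as failure up to day 6. When 4.6 is followed, the child fails under both texts through different components. A gap remains only if the prescription is late, is not made, or is not made by a study clinician.

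**Appendix A.** A reader might infer that the reported failures will be a different endpoint. The documents do not support this. SAP 10.2 describes the tables as candidates for the manuscript, and SAP 6.1 defines the endpoint and names the forms it is calculated from. Table 2 has its own total row, and the reason rows are a breakdown beneath it. Wrong rows make the breakdown fail to match the total but do not change the total. Table 4 also has a separate total, but there the SAP supplies no definition behind it.

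The prolonged-stay row may add few or no failures. Under Protocol 4.6, discharge criteria are met when no failure criterion is present, and logistical delays are exempt. In Table 4 the antibiotic-change and re-admission rows may record consequences of relapse, since Protocol 4.6 sends relapsed children to hospital for second-line therapy. They are nevertheless labelled as criteria.

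**Size.** A reader might want to move a few children in one arm only and quote the shift. Nothing supports a one-sided shift: clinical assessors are blinded, and one definition would apply to both arms.

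What stands: the SAP 6.1 sentence against its own windows, the two wording differences in Protocol 5.1, the missing relapse definition in the SAP, and shells whose rows cannot be filled from the definitions.

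**Conclusion.** The inconsistencies are real and should be removed, but no effect on the primary result has been shown. The most consequential is internal to SAP 6.1, because read literally it turns unresolved chest-indrawing before day 6 into failure. The windows listed in the same section, and in Protocol 3 and 5.1, make it unlikely that this was meant. The vomiting difference is mostly absorbed by the antibiotic-change criterion. The persistence wording affects only indrawing that resolves and returns by day 6. The Table 2 mismatches affect the breakdown of reasons. The relapse gap is more open, because the SAP has nothing to set against Table 4.

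The number of children affected cannot be derived from the documents. The arithmetic shows only that, with a relative margin, the definition sets the absolute margin and so can decide a close result without favouring either arm. That rests on assumed counts, an unadjusted interval and complete data for 950 per arm.

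**What to change.** Before unblinding, and decided by people who have not seen outcomes by arm:

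1. Reconcile Protocol 3, Protocol 4.6, Protocol 5.1 and SAP 6.1 into one dated definition of treatment failure. SAP 6.1 cannot serve as the reference unedited. The vomiting and temperature criteria bear on second-line treatment, so which wording applies is for the sponsor to settle.
2. Amend the closing sentence in SAP 6.1 so that each criterion counts only in its stated window, and say which criteria enter the day 2 and day 4 rates.
3. State the relapse definition in SAP 6.2, consistent with Protocol 5.1.
4. Rebuild Appendix A Tables 2 and 4 row by row from the reconciled definitions, so that every failure or relapse has a reason row and no row lacks a criterion behind it.

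The cost is a wording and table-shell correction, plus ethics approval of the protocol wording change, which the protocol requires for any amendment. Sample size and visit schedule are unaffected.
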